## Abstract

**Background:**

This paper presents the study protocol for a pragmatic randomised controlled trial to evaluate the impact of a school based program developed to prevent teenage pregnancy. The program includes students taking care of an Infant Simulator; despite growing popularity and an increasing global presence of such programs, there is no published evidence of their long-term impact. The aim of this trial is to evaluate the Virtual Infant Parenting (VIP) program by investigating pre-conceptual health and risk behaviours, teen pregnancy and the resultant birth outcomes, early child health and maternal health.

**Methods and Design:**

Fifty-seven schools (86% of 66 eligible secondary schools) in Perth, Australia were recruited to the clustered (by school) randomised trial, with even randomisation to the intervention and control arms. Between 2003 and 2006, the VIP program was administered to 1,267 participants in the intervention schools, while 1,567 participants in the non-intervention schools received standard curriculum. Participants were all female and aged between 13-15 years upon recruitment. Pre and post-intervention questionnaires measured short-term impact and participants are now being followed through their teenage years via data linkage to hospital medical records, abortion clinics and education records. Participants who have a live birth are interviewed by face-to-face interview. Kaplan-Meier survival analysis and proportional hazards regression will test for differences in pregnancy, birth and abortion rates during the teenage years between the study arms.

**Discussion:**

This protocol paper provides a detailed overview of the trial design as well as initial results in the form of participant flow. The authors describe the intervention and its delivery within the natural school setting and discuss the practical issues in the conduct of the trial, including recruitment. The trial is pragmatic and will directly inform those who provide Infant Simulator based programs in school settings.

**Trial registration:**

ISRCTN24952438

## Background

The social and financial cost to the individual and to society of unintended pregnancy is substantial and giving birth as a teenager is associated with a higher risk of negative consequences for both the young mother and child [1,2]. In developed countries teenage motherhood tends to be associated with low social and economic circumstances, and high risk behaviours such as drinking, smoking and drug use [3-6]. Although a small minority of teenage mothers in late teenage years have access to good social support and financial resources, most teenage mothers and their children represent high need clients for health and other social services [3,7]. In most states in Australia, child, family, community health and social services use teenage motherhood as a marker for providing increased services and as a referral criterion for access to targeted family support programs [8-10].

The Virtual Infant Parenting (VIP) Program is a school-based pre-conception program originally developed by the Swan Hills Division of General Practice in conjunction with the North Metropolitan Health Service (Perth, Western Australia) in a preventive response to high rates of teenage pregnancy across their region [11,12]. The VIP Program was an adaption of the American program known as 'Baby Think It Over'^® ^[13]. The program includes a series of education sessions and utilises an Infant Simulator, a life-like model that is programmed to replicate the sleeping and feeding patterns of a six-week old infant. Baby Think It Over^® ^was created by 'RealityWorks'^® ^which manufactures and sells the Infant Simulators [13,14]. The Infant Simulator is an example of an approach used in "persuasion technology" or captology [15]. In 1997 the VIP Program was piloted in Western Australia with 300 'high-risk' participants aged 14-15 years. The findings from the pilot study showed the program to be effective in establishing a positive partnership between health care providers and adolescents [11,12]. Post intervention follow-up questionnaires at one week and three months showed participants to be enthusiastic about the program, to have good levels of program recall and attitudes inclined towards delaying pregnancy. Since the original pilot, the program has continued to be implemented by various Area Health Services and Divisions of General Practice in Western Australia with high level support reported from parents, Teachers and General Practitioners [16,17].

Infant Simulator based programs are widespread in United States, Puerto Rico, Canada, Mexico, United Kingdom, Republic of Ireland, Australia, New Zealand, Japan, Germany, Netherlands, Austria, Switzerland, Italy, Belgium, Denmark, Luxemburg, Costa Rica, El Salvador, Nicaragua, Panama, Poland, Iceland and Finland [18]. Despite their popularity there is limited evidence to suggest that Infant Simulator based pre-conception interventions are effective in achieving their aims. Program evaluation is limited to measuring short-term changes in attitudes, beliefs and self-reported behaviours. The results of published studies are inconsistent; some have shown shifts in participants' attitudes and beliefs and others have shown no such change [19-28]. The findings of these studies are also limited by sample size and the range of outcomes they examine. In addition, Infant Simulators are costly. Each Infant Simulator with the necessary accessories (breastfeeding device, nappies, clothing, student wrist band identifiers, baby sling, batteries etc) can cost approximately AUD$1,800 and they require ongoing maintenance as a result of continual use by students. Infant Simulator programs therefore represent a significant financial investment by education and health services.

One of the difficulties in developing and providing programs aimed at improving sexual health behaviours, reducing sexually transmitted infection and avoiding teenage pregnancy has been a lack of evidence about what works. Observational studies in adolescent pregnancy prevention (across settings) may overestimate positive program effects compared to randomised trials [29]. In a meta-analysis of randomised trials carried out in 2002, it was concluded that theory-based interventions have had little effect on sexual behaviour or in reducing teenage pregnancy [30]. In contrast, another review describes programs that have been successful in changing sexual behaviour in the United States, highlighting the importance of addressing the non-sexual antecedents of teenage pregnancy [31]. In 2005 a systematic review of school based teenage pregnancy prevention programs in the United States showed only modest and short term impacts on abstinence, with no program showing significant impact on teenage sexual activity [32]. The authors additionally note the paucity of such studies and list the difficulties associated with undertaking such trials. To date, the quality and quantity of evaluation remains an issue in determining the success of teenage pregnancy prevention programs.

We are not aware of any other randomised research or publications investigating the longer-term pregnancy and birth outcomes of participation in a school-based Infant Simulator program. This paper documents our study protocol and does so in a way that is consistent with the guidelines for the reporting of a randomised controlled trial and, in particular, the extension of the CONSORT statement for cluster randomised trials [33] and pragmatic randomised controlled trials as advised by Zwarenstein et al. 2008 [34].

### Aims of the Study

The VIP Program's overarching goal is to reduce the individual and population health burdens associated with early teenage parenthood and unintended pregnancy. This research study aims to evaluate the VIP program against its specific stated objectives. Both the VIP program objectives and the study hypotheses pertain only to the individual level and not to the school/cluster level.

### VIP Program Objectives

The specific objectives of the VIP program are to demonstrate that 13-15 year old girls participating in the VIP program will:

1. Delay pregnancy.

2. Have fewer unplanned births and/or induced abortions.

3. Develop and maintain health sustaining behaviours before and during pregnancy.

4. Avoid health risk behaviours associated with an increased risk for low birth-weight children (e.g. smoking during pregnancy).

5. Improve knowledge, awareness and access to appropriate health care and other community supports for pregnant teenagers.

6. Have healthier early maternal and child health outcomes (for those that do have a live birth during their teenage years).

### Study Hypotheses

Relative to the non-intervention arm, participants in the experimental arm of the study will have:

1. A reduction in rates of teenage births.

2. A reduction in teenage induced abortion rates.

3. Higher self-efficacy to make informed decisions relating to pregnancy, by understanding the responsibilities associated with having a child through the virtual parenting experience.

4. An increased knowledge and/or use of services and resources relating to having a child, in the areas of nutrition, exercise, immunisation, contraception, body image, sexual and mental health, prevention of injury, smoking, alcohol and illicit drugs, SIDS, postnatal depression and breastfeeding.

5. Healthier child and maternal health outcomes (as measured by birth weight, complications in pregnancy and post natal depression).

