#### Maternal and Child Health Outcomes

In addition to tracking a live birth outcome via data linkage, maternal and child health outcomes are being collected for study participants who give birth during the Trial period.

Birth and early child health outcomes are obtained from the midwives data collection. Specifically, details regarding pregnancy complications, smoking status during pregnancy, plurality, gender, the child's birth weight, time to establish unassisted regular breathing, resuscitation method used (if applicable), Apgar scores at one and five minutes, estimated gestation, mode of separation (e.g. transferred or went home), adoption status, birth defects or birth trauma, any deaths of participants and still births are collected.

Maternal health and wellbeing and child health is further assessed via a post-birth interview conducted at the participant's home six months after giving birth (first child only). A strict protocol is adhered to for contacting participants. The contact details of the participants are accessed though their birth records. To organise a home interview post birth, the research team first writes to the local child health nurse and requests that the nurse contact the participant seeking their consent for interview. Once that consent is given, an interviewer from the research team with child health qualifications contacts the participant to arrange the interview. The interviewer is 'blind' as to whether the participant is from the intervention or control arm of the study. The interviewer assesses: pre-conceptual health and risk behaviours, folate supplementation, injury prevention and immunisation awareness, postnatal depression (Edinbourgh Scale) and psychological distress (K10); SIDS risk factor awareness; immunisation status; breastfeeding; awareness and uptake of health and other community supports; perceived level of support; and recall of specific VIP Program elements.

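### Hypothesis 5 claims a between-arm effect on outcomes seen only in participants who give birth, a group the program is meant to change, so that contrast is not randomised and can be biased either way

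*Protocol article*

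**What the plan says.** All references are to the Protocol article.

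- **Study Hypotheses.** The list opens "Relative to the non-intervention arm, participants in the experimental arm of the study will have". Item 1 is "A reduction in rates of teenage births", item 2 expects fewer induced abortions, and item 5 is "Healthier child and maternal health outcomes (as measured by birth weight, complications in pregnancy and post natal depression". Item 5 carries no caveat that sets it apart from items 1 and 2.
- **VIP Program Objectives.** Objective 1 is to delay pregnancy. Objective 6 concerns maternal and child health and is limited to "for those that do have a live birth during their teenage years". Aims of the Study says the trial evaluates the program against these objectives.
- **Maternal and Child Health Outcomes.** The section states that "maternal and child health outcomes are being collected for study participants who give birth during the Trial period". On sources, "Birth and early child health outcomes are obtained from the midwives data collection"; stillbirths are among the items listed. Postnatal depression comes from a "post-birth interview conducted at the participant's home six months after giving birth (first child only"), for which separate consent is sought.
- **Planned analyses for the Primary Outcome.** Births, abortions and pregnancies are covered. No analysis is given for hypothesis 5.
- **Discussion.** Participation bias at enrolment is acknowledged, as is statistical control for baseline differences between the arms. Selection by giving birth is not mentioned.

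**The concern.** Hypothesis 5 is worded as an effect of allocation, but its measures are available only for participants who give birth. The program is expected to reduce that group, so membership is itself a possible effect of the intervention. If the births it prevents come mainly from lower-risk girls, the remaining mothers in the intervention arm will on average be at higher risk, and the program can look harmful to infants. The reverse pattern can look protective. Neither would be an effect on maternal or child health.

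At stake is how hypothesis 5 may be interpreted: whether a difference among mothers can be reported as something the program caused.

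**Working it through.** **1. How the text defines the comparison.** The hypothesis list sets arm against arm. Objective 6 and the outcome section set the population as those who give birth. Hypotheses 1 and 2 and objective 1 say the program will alter who gives birth and when. The among-mothers contrast escapes selection only if the program does not change who gives birth, which contradicts hypothesis 1, or if the births prevented are unrelated to outcome risk, which the article nowhere claims.

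**2. Routes of selection.**
- Births prevented.
- Abortion. Sample Size Calculation expects 10.8% abortion within 16.8% known pregnancy, so 10.8/16.8 = 64% of known pregnancies end in abortion. If that share were 60% with pregnancies unchanged (assumed), births would be 16.8% × 0.40 = 6.7% instead of 6.0%, about 12% more. The pool of mothers can grow as well as shrink.
- For postnatal depression only, consent to the interview.

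**3. Expected births.** The plan gives no figure for hypothesis 5. Inputs from the article are a 6% control live-birth rate and 1,567 control and 1,267 intervention participants. The planned 25% reduction refers to pregnancies; applying it to births is an assumption.
- Control: 0.06 × 1,567 = 94.
- Intervention: 0.06 × 0.75 × 1,267 = 0.045 × 1,267 = 57.

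**4. Illustration A (risk inputs assumed; no effect on infant health within a risk group).** In the control arm, 60% of births come from a group with 12% low birth weight and 40% from a group with 5%. The program prevents 15% and 40% of births in these groups.
- Births remaining, as a share of control births: 0.6 × 0.85 + 0.4 × 0.60 = 0.51 + 0.24 = 0.75, a 25% reduction.
- Low birth weight among births, control: 0.6 × 0.12 + 0.4 × 0.05 = 9.2%.
- Low birth weight among births, intervention: (0.51 × 0.12 + 0.24 × 0.05)/0.75 = 0.0732/0.75 = 9.8%.
- Low-birth-weight births per 1,000 participants: 60 × 0.092 = 5.5 in control and 60 × 0.0732 = 4.4 in intervention.

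The two summaries move in opposite directions although infant health within each risk group is unchanged.

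**5. Illustration B (direction; inputs assumed).** Half of control mothers are high risk, with adverse outcome rates of 20% (high risk) and 5% (low risk). A quarter of births are prevented, with no effect on the outcome itself. Control rate: 0.5 × 0.20 + 0.5 × 0.05 = 12.5%.

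| Births prevented from | Intervention rate among births | Spurious difference |
|---|---|---|
| low-risk girls only | (0.50 × 0.20 + 0.25 × 0.05)/0.75 = 15.0% | +2.5 points |
| both in proportion | 12.5% | 0 |
| high-risk girls only | (0.25 × 0.20 + 0.50 × 0.05)/0.75 = 10.0% | −2.5 points |

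With high-risk shares from 30% to 70%, the spurious difference runs from −3.5 to +3.5 points.

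**6. Size against sampling error.** Standard error of a difference in proportions with 94 v 57 births, before any allowance for clustering:
- Illustration A: √(0.092 × 0.908/94 + 0.0976 × 0.9024/57) = 4.9 points. The bias of 0.6 points is about one-ninth of this.
- Illustration B, low-risk only: √(0.125 × 0.875/94 + 0.15 × 0.85/57) = 5.8 points. The bias of 2.5 points is under half of this.

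**The case against.** **No analysis of hypothesis 5 is fixed.** The analysis section covers the primary outcome only, and the handling of secondary outcomes is commonly left to an analysis plan that is not shown. A reader might infer that the article commits to a causal among-mothers analysis. It does not: no denominator or model is stated. What remains is that the between-arm claim and its restriction to those who give birth are already published, without a caveat.

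**Conditioning need not bias.** A reader might infer that the two groups of mothers must differ. Illustration B shows otherwise: proportional prevention gives 12.5% v 12.5%. The supportable statement is that the contrast can be biased, and that randomisation does not protect it.

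**Not only live births.** A reader might take all the outcomes to be confined to live births, as objective 6 says. The midwives collection covers all births and stillbirths are listed, so the condition is giving birth. The argument is unchanged.

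**The illustrated bias is small.** This stands. It is a fraction of a standard error, and it needs assumed risk strata and strongly unequal prevention.

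**An all-participant rate answers another question.** This also stands. Objective 6 asks about health among those who do give birth. A program that only reduced births would lower the all-participant rate with no benefit to any infant, partly restating hypothesis 1. Birth weight as a continuous measure has no value for participants without a birth. The rate can supplement the among-mothers comparison but cannot replace it.

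**Enrolment already weakens randomisation.** Students knew their arm before consenting, and participation was 58% v 45%. The article acknowledges this and lists entry covariates. Adjusting for them among mothers may reduce the selection by birth, but would not restore a randomised comparison.

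**Conclusion.** The point holds as a minor one. Hypothesis 5 states an arm effect on outcomes restricted to participants who give birth, while hypotheses 1 and 2 expect the program to change that group, and the article does not acknowledge the conditioning. A contrast among mothers is not a randomised comparison. It can be biased in either direction if prevented births are related to outcome risk. Postnatal depression has the further filter of interview consent.

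The documents do not show that bias will occur or how large it would be. Every size given here rests on assumed risk groups, assumed patterns of prevention and a 25% reduction moved from pregnancies to births. Under those assumptions the shift is 0.6 points in illustration A and at most 3.5 points across the patterns in illustration B, against a standard error of about 5 points in illustration A. The consequence is for what hypothesis 5 can support. The primary outcome is untouched.

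**What to change.** 1. State that comparisons among mothers (birth weight, complications, postnatal depression) are descriptive and non-randomised, adjusted for the entry covariates already collected, and do not by themselves support a causal claim for hypothesis 5. Say whether stillbirths are in the denominator, and note the added interview-consent step for postnatal depression.
2. For outcomes held in linked records, also report by arm the cluster-adjusted proportion of all participants with an adverse birth outcome by age 20, for example low birth weight or a complicated pregnancy recorded at birth. The definition needs to be set in advance.
3. Read that proportion alongside the birth rate, because it mixes fewer births with healthier births. State that it remains subject to the differential consent described in the Discussion.

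The cost is analysis wording and one extra table. No new data are needed, since linkage already follows all participants. The all-participant measure requires a yes/no definition that the article does not give for birth weight, and it supplements objective 6 without answering it.

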## Methods and Design

### Trial Design

The evaluation design for the VIP Program is a pragmatic school-based cluster randomised controlled trial. Although the VIP Program is targeted at an individual level, a school-based clustered design was considered necessary to limit contamination with control participants. In previous pilot studies there was anecdotal evidence of students organising social get togethers such as "sleepovers" while taking care of Infant Simulators and thus contamination was a real concern. Cluster randomisation additionally allowed pragmatic evaluation of the implementation of the VIP Program in schools from a process point of view.

### Setting

This pragmatic trial was conducted in all participating schools physically based within the catchment areas of the three metropolitan health services encompassing the entire metropolitan region of Perth, Western Australia. The East, North and South Metropolitan Health Services employ the School Health Nurses who delivered the VIP Program. Perth is the fourth largest city in Australia with the metropolitan region having a population of 1.5 million [35]. The recruitment and intervention period of the study commenced in February 2003 and was completed in May 2006 with the follow-up period expected to be completed in mid 2012.

### Recruitment

#### Cluster level (school)

All metropolitan government and independent high schools in metropolitan Perth (excluding Catholic schools) were invited to participate in the study. Overall, 57 of the 66 invited schools enrolled in the program (86%). The government school participation rate was higher (51/54 or 94%) than that for non-government schools (6/12 or 50%) due to the limited availability of School Health Nurses for program implementation in private schools. Twenty-nine schools were randomly allocated to each arm of the study.

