#### Individual level (Student)

In each of the intervention and non-intervention trial arms, all females in either year 9 or 10 were approached to participate. Male students, and female students who were pregnant or already had a child, were not actively recruited or enrolled into the study. Males were excluded from the trial due to the primary outcome being teenage pregnancy and birth outcomes along with an inability to accurately and ethically determine the male donor/contributor to a pregnancy.

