### Randomisation

Randomisation was performed at the cluster level with a table of random numbers (without blocking, stratification or matching) by a researcher who was blind to the identity of the schools. After initial recruitment one government school was excluded from the intervention arm after it was detected that the study's Individual Recruitment Protocol was not adhered to. Individual participants were not blinded to their group assignment and upon giving consent were aware whether they were participating in the VIP intervention or control arm of the Trial.

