### Consent

Written active consent from both a parent/guardian and the participant was required by the Ethics Committee's to access data for the longitudinal component of the research study until the participants reached the age of 20 (intervention and control arms). The consent specifically included permission for the research team to access data relating to pregnancy from hospital administrative records and abortion clinics. In a bid to maximise participation rates, four additional research staff were recruited to support School Health Nurses in their recruitment efforts. Despite best practice recruitment procedures, approved incentives and significant time and resources, the participation rates at the student level remained relatively low (Refer to Table 1). This is considered further in the discussion section of this paper.

**Table 1 T1:** Participation rates at the Individual level

Study Arm	Students approached	Consented & participated	Participation rate	Mean participants per cluster	Participant range per cluster
Intervention	2177	1267	58%	47	3-166
Non-intervention	3510	1567	45%	54	13-163

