Recruitment bias becomes a threat to the external validity if there are systematic differences in the characteristics of participants in the intervention and control arms that are associated with the exposure or outcome variables. Unfortunately, the study was unable to collect information from the students who did not participate or the parents who failed to provide consent. Therefore we can only anticipate differences between participants and non-participants based on the best available evidence. In general epidemiological studies, participants are more likely to be of higher socioeconomic status, employed, married and of better health status. Further, in studies of risk behaviours, those engaged in those behaviours are less likely to participate [49] The requirement for active parental consent has been associated with the lesser representation of ethnic minorities, students having problems at school and students already engaged in or at risk of problem behaviours [52,54]. So while the study cannot control for systematic differences between participants and non-participants, it can statistically control for potential baseline differences between the intervention and control groups. The following data has been collected by the Trial to investigate and control for potential confounders: socio-economic status, family type, whether the participant had ever had sexual intercourse, had ever had responsibility for caring for a baby, reported importance and intention of going to University or further education, level of psychological distress, and smoking, drug and alcohol use. These variables were measured at the time of entry into the Trial. Additionally each participant's educational attainment data has been linked to the Trial data to enable controlling for academic success.

In conclusion although the pragmatic nature of the trial and the low participation rates will provide some complexities for the analyses, the results will have international significance and advance the evidence to inform school based teen pregnancy prevention programs.

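### The school counts do not reconcile (57 enrolled, 29 + 29 allocated, 27 + 29 implied by Table 1), and differences between arms are labelled a threat to external rather than internal validity

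*Protocol article*

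**What the plan says.** School counts appear in four places in the protocol article.

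- Abstract, Methods and Design: "Fifty-seven schools (86% of 66 eligible secondary schools) in Perth, Australia were recruited to the clustered (by school) randomised trial". The same sentence describes the allocation as even.
- Recruitment, Cluster level (school): again 57 of 66, made up of 51 of 54 government and 6 of 12 non-government schools. The paragraph ends: "Twenty-nine schools were randomly allocated to each arm of the study".
- Randomisation, on a loss that followed the first stage of enrolment: "one government school was excluded from the intervention arm after it was detected that the study's Individual Recruitment Protocol was not adhered to". No other lost school is mentioned in the text.
- Consent, Table 1, column "Mean participants per cluster": 47 in the intervention arm (1,267 participants) and 54 in the control arm (1,567 participants).

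On validity, the Discussion states: "Recruitment bias becomes a threat to the external validity if there are systematic differences in the characteristics of participants in the intervention and control arms", where those differences are related to exposure or outcome. Elsewhere the Discussion says that internal validity was maximised, citing nurse training, the manual and fixed simulator programming. It also reports that girls knew before taking part whether they would have the simulator, and that this made recruitment easier in the intervention arm (58% v 45%).

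**The concern.** Schools are the unit of randomisation, so the numbers randomised, excluded and analysed in each arm are the basis for judging whether the comparison is as randomised. The article presents participant flow as its initial results and claims consistency with the CONSORT extension for cluster trials. A conflict in these counts is therefore a fault in something the article sets out to report, not a detail left to a fuller document.

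The one reported exclusion followed a breach of the individual recruitment procedure and affected the intervention arm only. A reader needs to know whether it was the sole loss and whether the result depends on it.

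The validity label matters for a related reason. Girls were recruited after their school had been allocated and knew their arm. If that produced arms that differ on factors related to pregnancy, the estimated effect is confounded. Calling this a question of external validity suggests that only generalisability is affected.

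**Working it through.** **Inputs.** 57 schools enrolled (51 + 6) of 66 invited; 29 allocated per arm (Recruitment, Cluster level); one intervention school excluded (Randomisation); 1,267 and 1,567 participants with means of 47 and 54 per cluster (Table 1).

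**1. The plan's own figures.** 51 + 6 = 57, and 57/66 = 86.4%, so 57 and 86% agree with each other. The participation rates also reproduce: 1,267/2,177 = 58.2% and 1,567/3,510 = 44.6%.

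**2. Allocated against enrolled.** 29 + 29 = 58. More schools cannot be randomised than were enrolled, so 58 and 57 conflict as worded. Also, 57 is odd and cannot split exactly evenly.

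**3. Schools implied by Table 1.** Number of schools = participants / mean per cluster, allowing for rounding of the mean to a whole number.

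- Intervention: 1,267/47 = 26.96; range 1,267/47.5 = 26.67 to 1,267/46.5 = 27.25. The only whole number is 27.
- Control: 1,567/54 = 29.02; range 1,567/54.5 = 28.75 to 1,567/53.5 = 29.29. The only whole number is 29.
- Total: 27 + 29 = 56.

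**4. Possible reconciliations.**

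- *58 randomised, 57 after the exclusion (28 + 29).* This keeps 29 per arm, and keeps 57 if it is relabelled as a count after exclusion. The intervention mean would then be 1,267/28 = 45.25, that is 45, not 47.
- *58 randomised, and Table 1 correct (27 + 29).* This needs two intervention schools lost. The text reports one.
- *57 randomised as 28 + 29, 56 after the exclusion (27 + 29).* Table 1 then fits (1,267/27 = 46.9; 1,567/29 = 54.0), and 57 and 86% stand as enrolment figures. The statement of 29 in each arm is wrong.
- *57 randomised as 29 intervention + 28 control, then 28 + 28.* Table 1 would show 45 and 56 (1,567/28 = 55.96), so this fits neither row.

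No set of counts satisfies every statement.

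**5. The validity label.** The quoted sentence defines the threat as a difference between the intervention and control participants. Such a difference biases the comparison between arms, which is internal validity. The same paragraph goes on to plan adjustment for baseline differences between the arms, which is the remedy for an internal-validity problem. The measures cited for internal validity (training, manual, programming) concern delivery of the intervention and do not bear on recruitment after allocation.

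**The case against.** The strongest reply is that this is one slip in the text. If 57 schools were randomised as 28 and 29, then 57, 86%, 47 and 54 are all correct, the single exclusion explains Table 1, and only the sentence giving 29 per arm needs changing. Figure 1, the participant flow, is not shown and may account for every school. This stands to the extent that nobody should assume 57 is the wrong figure. It does not remove the conflict: on this reading the stated allocation is still wrong, and a figure cannot make the printed sentences agree.

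On validity, the article is open about the problem. It names low participation as the main limitation, reports 58% v 45%, and lists baseline confounders and linked educational attainment for adjustment. That is fair, and it means the label is wrong rather than the problem hidden. The label should still be corrected, because the claim of maximised internal validity otherwise goes unqualified.

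Finally, analysis sets and sensitivity analyses may be defined in an analysis plan that is not shown. That is right: their absence from the article is no fault, and the sensitivity analysis below is a recommendation that follows from the reported exclusion.

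**Conclusion.** The point holds for the school counts and for the validity label. At least one of 57 enrolled, 29 + 29 allocated and the mean of 47 is wrong or wrongly described. The size is one school at each stage: 57 or 58 randomised, and 56 or 57 analysed. This rests on reading the Table 1 mean as participants divided by schools, rounded to a whole number; the 27 is inferred and not printed. The number of girls in the excluded school is not given, so the effect of leaving it out cannot be sized.

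A reader might infer more than the documents support:

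- *That 57 already omits the excluded school, so enrolment was 58 of 66.* The article calls the 57 schools enrolled or recruited, and 57 randomised as 28 + 29 fits Table 1.
- *That a second intervention school was certainly lost.* This follows only if both 29 + 29 and the mean of 47 are correct.
- *That girls were selectively approached in the intervention arm.* The article says "In each of the intervention and non-intervention trial arms, all females in either year 9 or 10 were approached to participate", while Table 1 gives 2,177/27 = 81 approached per intervention school and 3,510/29 = 121 per control school. The gap is unexplained. However, no enrolment figures are given, randomisation was not stratified, and participants per school range from 3 to 166. The limit of five girls per week needs only 1,267/27/5 = 9.4 weeks per school on average, against recruitment over two years in most schools. Any recalculated intervention participation rate would rest on assuming equal school sizes.
- *That the Discussion argues a direction of bias between arms from 58% v 45%.* It does not. It reports easier recruitment in one arm and takes the differences between participants and non-participants from the literature.

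**What to change.** 1. State for each arm the number of schools randomised, excluded (with reasons) and analysed, and correct whichever of 57 (86%), 29 + 29 or 47 is wrong. The trial's allocation records should decide this; 58 of 66 should not be presumed. Cost: a check of records and a few corrected figures.
2. Add a sensitivity analysis of the primary outcome by random allocation that includes the excluded school's girls where consent is valid. Cost: one extra model run, limited to those with valid consent.
3. In the Discussion, name systematic differences between arms, arising from recruitment after allocation with girls aware of their arm, as a threat to internal validity. Qualify the statement that internal validity was maximised so that it covers delivery of the program only. Cost: two sentences.
4. If school records allow, give the eligible girls per arm beside those approached, so that the 81 v 121 gap can be understood. This is a request for information, not a correction.
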